**Introduction**

Compared with transperitoneal laparoscopic approach, retroperitoneoscopic approach has many advantages in urological surgery, such as shorter puncture path, shorter operative time, less blood loss, less postoperative pain, and faster recovery[1-4]. However, restricted to the retroperitoneal anatomy, the limited working space can make the procedure technically challenging, higher insufflation pressures (20–25 mmHg) of CO_2_ is needed to create a larger working space[5, 6]. More CO_2_ is absorbed into the blood, causing harm to the human internal environment.

Propofol-based total intravenous anesthesia (TIVA) and sevoflurane inhalation anesthesia are two general anesthesia techniques commonly used in clinical practice. Compared with inhalation anesthesia, whether TIVA can provide better postoperative quality of recovery is influenced by the type of surgery[7-9]. The Global Quality of Recovery- 40 (QoR-40) questionnaire was specifically designed to measure the health status of patients after surgery and anesthesia, and it involves 5 dimensions: physical comfort, physical independence, emotional state, psychological support and pain[10]. On the strength of its reliability and validity, QoR-40 has a broad clinical application[11, 12] . Peripheral inflammatory factors can lead to inflammatory reactions such as vasodilation, increased permeability, leukocyte exudation, and even increase the permeability of the blood-brain barrier. Inflammatory factors enter the central nervous system, neurons are damaged or die, resulting in brain tissue damage. By measuring and comparing the levels of perioperative inflammatory factors, we can predict the postoperative recovery of patients[13, 14].

Therefore, the objective of our study is to compare the effects of TIVA and inhalation anesthesia on the quality of recovery by using the QoR-40 questionnaire, and the levels of inflammatory factors in patients undergoing urological retroperitoneoscopic surgery.

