***Eligibility criteria***

***Inclusion criteria***

Patients who are 18-65 years old with American Society of Anesthesiologists (ASA) physical status I-III and scheduled for Urological Retroperitoneoscopic Surgery under general anesthesia will be eligible for inclusion.

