***Outcomes***

***Primary outcomes***

The primary outcome of this study is global Quality of Recovery-40 (QoR-40) score on POD 1. The QoR-40 contains 40 items assessing five dimensions of recovery: emotions, physical comfort, psychological support, physical independence, and pain, which scores range from 40 to 200. QoR-40 has been widely used in clinical practice and research for various surgical types and anesthesia techniques.

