***Sample size estimation***

The primary outcome that will be assessed in this study is the QoR-40 score on postoperative day (POD) 1. Previous studies reported that the minimal clinically important difference (MCID) of QoR-40 score was 6.3 points[10], based on our institutional data, the Standard Deviation was 9.3 points. Based on this assumption, 36 patients in each group would be required with a power of 80% and at an α level of 0.05. To allow for 10% possible dropouts, a total of 80 patients (n = 40 in each group) will be enrolled. The sample size is calculated using the PASS software (version 15.0.5, NCSS, LCC, Kaysville, UT).

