***Statistical analysis***

The demographic data and baseline characteristics will only be expressed using descriptive statistics and will not be compared between groups. According to the data distribution, continuous data will be expressed as means and standard deviations, or median and interquartile ranges. Categorical data will be presented as numbers and percentages. The differences between groups will be analyzed by independent t-test, repeated measures analysis of variance, or Mann Whitney rank sum test, Chi-squared test, or Fisher exact test as appropriate. All data will be analyzed using the SPSS software (version 21.0; IBM SPSS, Chicago, IL) by the independent statistician. A two-sided P value < 0.05 indicates a statistically significant difference.

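### The POD 1 QoR-40 comparison uses unadjusted tests although preoperative QoR-40 is collected, so precision available at almost no cost is given up

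*Protocol*

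**What the plan says.** Protocol, Primary outcomes: "The primary outcome of this study is global Quality of Recovery-40 (QoR-40) score on POD 1". This is one score at one time point.

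Protocol, Statistical analysis: "The differences between groups will be analyzed by independent t-test, repeated measures analysis of variance, or Mann Whitney rank sum test", followed by tests for categorical data, each to be used as appropriate. No covariate and no stratifying factor is named. For a continuous outcome at a single time point, the tests on offer are the t-test and the Mann-Whitney test, both unadjusted. The threshold is "A two-sided P value < 0.05 indicates a statistically significant difference".

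Protocol, Appendix A, Table 1: QoR-40 is marked at the preoperative visit and again at 24, 48 and 72 hours. Allocation takes place 2 hours before surgery, after that visit, so the preoperative score is a true pre-randomisation measurement.

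Protocol, Sample size estimation: "the minimal clinically important difference (MCID) of QoR-40 score was 6.3 points"; "based on our institutional data, the Standard Deviation was 9.3 points"; "36 patients in each group would be required with a power of 80% and at an α level of 0.05".

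Two further statements bear on the operation performed. The Introduction says that "whether TIVA can provide better postoperative quality of recovery is influenced by the type of surgery". The Inclusion criteria admit anyone "scheduled for Urological Retroperitoneoscopic Surgery under general anesthesia will be eligible for inclusion", without separating procedures.

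**The concern.** The trial measures its primary endpoint before randomisation and then, as written, does not use that measurement in the primary comparison. Whatever part of the POD 1 variation reflects how patients scored before surgery stays in the error term, and any chance difference between the arms in preoperative score stays in the estimated effect. With 36 evaluable patients per arm and planned power only just above 80%, a narrower interval would be worth having. The data are already scheduled, so the gain needs no extra patient, visit or instrument.

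The stake is efficiency. Type I error, unbiasedness and the stated sample size are not in question.

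**Working it through.** **Inputs.** Difference 6.3 points, SD 9.3 points, two-sided α 0.05, 36 per arm and 10% dropout, all from the protocol. The share of POD 1 variance explained by a covariate (R²) is not given, so a range is assumed.

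**1. The plan's own figure.** The standardised difference is 6.3/9.3 = 0.677. The two-sample t-test needs 35.19 per arm for 80% power, rounded up to 36. Allowing for dropout, 36/0.9 = 40 per arm, 80 in total. Both figures reproduce. At 36 per arm the noncentrality is 6.3/(9.3·√(2/36)) = 6.3/2.192 = 2.874 on 70 df, giving power of 80.9%. The 95% CI half-width is 1.994 × 2.192 = 4.37 points. With all 40 per arm evaluable, power is 84.9%.

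**2. Adding preoperative QoR-40.** With k covariate terms and N = 72, the residual variance becomes 9.3²·(1 − R²). The variance of the adjusted difference is also inflated, on average, by f = 1 + k/(N − k − 3), because covariates are never perfectly balanced. The df are 70 − k. For k = 1, f = 1 + 1/68 = 1.0147 and df = 69. The noncentrality is 2.874/√(1.0147·(1 − R²)).

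| Assumed R² | Noncentrality | Power at 36 per arm | 95% CI half-width (points) |
|---|---|---|---|
| Unadjusted | 2.874 | 80.9% | 4.37 |
| 0 | 2.853 | 80.3% | 4.41 |
| 0.05 | 2.927 | 82.3% | 4.29 |
| 0.10 | 3.007 | 84.3% | 4.18 |
| 0.25 | 3.294 | 90.1% | 3.81 |

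A simulation of this model (40,000 trials per row, normal data) gave 80.4%, 82.1%, 84.5% and 90.3% for the four adjusted rows, in agreement. The break-even R² is about 0.015.

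**3. Adding procedure class.** Three classes need two indicators. For those alone, k = 2, f = 1 + 2/67 = 1.0299 and df = 68. Power is 79.7%, 81.7% and 83.7% at R² of 0, 0.05 and 0.10. If procedure is not prognostic, the cost is 80.9 − 79.7 = 1.2 points. With preoperative QoR-40 as well (k = 3, f = 1 + 3/66 = 1.0455) and a joint R² of 0, power is 79.1%.

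**4. Chance imbalance in procedure.** Suppose one class holds 30% of patients. The SD of the difference in its share between arms is √(2·0.3·0.7/36) = 0.108, so the arms differ by more than 10 percentage points in about 35% of trials. If that class differed in mean QoR-40 by 6.3 points, a 10-point imbalance would move the estimate by 0.1 × 6.3 = 0.63 points, against a standard error of 2.19. The unadjusted test and interval already allow for this kind of error.

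**5. Effect modification.** With two equal strata of 18 per arm, the standard error of an interaction is 9.3·√(4/18) = 4.38. Power for a 6.3-point interaction is Φ(6.3/4.38 − 1.96), about 30%.

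**The case against.** The strongest reply is that nothing is wrong. A t-test in a randomised trial is valid, matches the method used to size the trial, and reaches the stated power on the protocol's own inputs. Choice of covariates often sits in a statistical analysis plan, which is not shown here. The gain rests wholly on an R² that the documents do not give; if patients awaiting elective surgery score much alike beforehand, it could be small.

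Most of this stands, and it keeps the point minor. It does not remove it. The protocol is not silent on the comparison: it lists the tests, and those that fit a single POD 1 score are unadjusted. Repeated measures analysis of variance is also listed, but the protocol does not say that it takes in the preoperative score or that it serves the primary outcome. The trade is lopsided: about half a point of power at worst, against several points at a modest R².

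A reader might also infer something stronger: that the protocol admits the effect depends on the operation, then contradicts itself by pooling operations, and so discards a known prognostic covariate. The documents do not support this, for three reasons.

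- The Introduction speaks of the anaesthetic effect differing by type of surgery, which is effect modification. Precision comes from a covariate that predicts the outcome, a different property. A model with procedure as a main effect and no interaction would not address that sentence.
- The sentence compares surgical settings. Of the three cited titles, two name pancreatectomy and total laparoscopic hysterectomy, and the third names no operation. This motivates a trial in one surgical setting, which is what the protocol sets up.
- Nothing in the protocol says that the procedure predicts QoR-40 within retroperitoneoscopic urology, and no procedure classes are defined.

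**Conclusion.** The point holds as an optional but worthwhile improvement. The primary comparison, as written, makes no use of a baseline measurement of the same scale that the trial already collects. Adjusting for it changes power at 36 per arm from 80.9% to about 80%, 82%, 84% or 90% for an assumed R² of 0, 0.05, 0.10 or 0.25. The CI half-width moves from 4.37 to between 4.41 and 3.81 points. These figures take the protocol's 6.3 and 9.3 points as given and assume a linear relation with the same slope in both arms; the R² values are assumptions.

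The case for procedure class is weaker. Its link to QoR-40 is not documented, and two indicators cost about one point of power if there is none. It should be secondary.

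**What to change.** State in the Statistical analysis section that POD 1 QoR-40 will be analysed by a linear model (ANCOVA) with group and preoperative QoR-40 as terms, reporting the adjusted difference with its 95% CI. Keep the unadjusted t-test as a sensitivity analysis.

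Optionally, add a prespecified sensitivity model that includes scheduled procedure in two or three classes, pooling sparse ones. In either case, describe the procedure mix by arm, so that readers can see which operations the pooled result represents. Any analysis of effect by procedure should be labelled exploratory.

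Fix the model and any classes before outcome data are seen by arm. Because the protocol plans an interim analysis, that means before the interim look as well as before unblinding.

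The cost is one or two sentences, one degree of freedom and about half a point of power if preoperative QoR-40 proves uninformative. Sample size, randomisation and visit schedule do not change. Recording procedure class adds one field already known before surgery.

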**Materials and methods**

This is a prospective, parallel, double-blinded, randomized controlled trial, which will be administered at the Guanyun People’s Hospital.

***Eligibility criteria***

***Inclusion criteria***

Patients who are 18-65 years old with American Society of Anesthesiologists (ASA) physical status I-III and scheduled for Urological Retroperitoneoscopic Surgery under general anesthesia will be eligible for inclusion.

***Exclusion criteria***

Patients who meet the following one or more exclusion criteria will be excluded from the study: (1) unplanned or emergency surgery; (2) those with mental illness, cognitive dysfunction, chronic pain disease, long-term use of sedative and analgesic drugs or alcohol abuse; (3) severe liver and kidney disease;(4) severe cardiopulmonary disease; (5) pregnant women and lactating women ;or (6) those who are allergic or contraindicated to the drugs used in the research.

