***Study implementation***

***Anesthesia and monitoring methods***

All patients will be fasting for 6-8 h and water deprivation for 2 h before operation, and will not receive any preoperative medication. Baseline blood pressure and heart rate will be obtained in the preoperative preparation area. After entering the operating room, patients will receive a standard monitoring including electrocardiography (ECG) and pulse oximetry (SpO2). An intra-arterial cannula will be placed in the radial artery for continuous arterial pressure measurement. Anesthetic depth will be measured using the Bispectral index. End-tidal carbon dioxide concentration (PetCO2) will be monitored after intubation. The participants will be divided into the total intravenous anesthesia group (group T) or the inhalation anesthesia group (group C) according to the allocation.

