***Secondary outcomes***

The secondary outcomes include QoR-40 score on POD 2 and POD 3, levels of proinflammatory cytokines (tumor necrosis factor-α, interleukin -1β, and interleukin -6), hemodynamic parameters, arterial and end tidal carbon dioxide pressure, pain scores at rest and while coughing, extubation time , length of PACU stay, ramsay sedation score on awakening, awakening time , adverse events (postoperative nausea and vomiting, headache, respiratory depression ,hypoxemia).

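### The exclusion list covers disturbers of the QoR-40 but names no infection, inflammatory disease or immune-active drug that would alter the cytokines compared under the same objective

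*Protocol*

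**What the plan says.** The Introduction of the protocol closes with an objective in two parts: quality of recovery by the QoR-40, "and the levels of inflammatory factors in patients undergoing urological retroperitoneoscopic surgery". Under Secondary outcomes the second part becomes "levels of proinflammatory cytokines (tumor necrosis factor-α, interleukin -1β, and interleukin -6". The QoR-40 on POD 1 is the only primary outcome, and the sample size rests on it alone.

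The Inclusion criteria take adults aged 18 to 65, ASA I to III, who are "scheduled for Urological Retroperitoneoscopic Surgery under general anesthesia will be eligible for inclusion". They set no limit by organ or indication.

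The Exclusion criteria have six items. Item 2 is "those with mental illness, cognitive dysfunction, chronic pain disease, long-term use of sedative and analgesic drugs or alcohol abuse". The items closest to the present point are "1) unplanned or emergency surgery" and "3) severe liver and kidney disease;(4) severe cardiopulmonary disease". The other two concern pregnancy or lactation, and allergy or contraindication to the study drugs.

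On sampling, the Data collection section gives cytokines at 2, 6 and 24 h after surgery. Appendix A, Table 1 marks those times and also the preoperative visit. The Statistical analysis section lists the t-test, repeated measures ANOVA, Mann-Whitney, chi-squared and Fisher tests. It states no covariate adjustment.

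**The concern.** Item 2 is a list of things that disturb a patient-reported recovery score. Nothing comparable protects the cytokine comparison. A patient with a current urinary infection, or one taking systemic steroids for an inflammatory disease, can satisfy every criterion and be enrolled. In such a patient the cytokine level, or its rise after surgery, may owe more to the disease or the drug than to propofol or sevoflurane.

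What is at stake is the precision and readability of a secondary outcome that the protocol places next to the QoR-40 in its objective. A handful of such patients among 80 widens the spread, and by chance they may fall unevenly between the arms. A statistical analysis plan could adjust for this but could not change who is enrolled. The protocol also does not say that infection status or steroid use will be recorded.

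**Working it through.** **1. The plan's own figure.** Inputs from Sample size estimation: difference 6.3, SD 9.3, power 80%, α 0.05 (two-sided, from Statistical analysis).
- Standardised effect: 6.3/9.3 = 0.677.
- Normal approximation: n = 2(1.960 + 0.842)²/0.677² = 34.2, so 35 per arm.
- Noncentral t: 35 per arm gives 79.8% and 36 gives 80.9%, so 36 is right.
- Dropout: 36/0.90 = 40 per arm, 80 in all.

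The figure reproduces. It uses only the QoR-40, so the present point does not touch it.

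**2. Does any passage close the gap?**
- Elective surgery only: limits acute infection, but not a planned operation in a patient with current infection.
- Severe liver, kidney or cardiopulmonary disease: a grade of organ disease, not an inflammatory state.
- Chronic pain and long-term analgesics: remove some patients with inflammatory disease, but not by virtue of the inflammation or of steroid use.
- "will not receive any preoperative medication" (Anesthesia and monitoring methods): stands in the sentence on fasting and is not an eligibility rule about long-term drugs.

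The gap stays open.

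**3. Loss of precision (assumed values).** The protocol gives no cytokine SD, no target difference and no prevalence of these conditions. Suppose a share f of patients has levels shifted by k within-group SDs on the log scale. The SD is then multiplied by √(1 + f(1−f)k²). For f = 0.10 and k = 2 that is √(1 + 0.09 × 4) = 1.166. Power of an unadjusted t-test with 36 per arm and a true effect of 0.677 SD (borrowed from the QoR-40):

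| Share affected | k = 1 | k = 2 | k = 3 |
|---|---|---|---|
| 0% | 80.9% | 80.9% | 80.9% |
| 5% | 79.1% | 73.8% | 66.0% |
| 10% | 77.5% | 68.1% | 55.8% |
| 20% | 74.9% | 60.0% | 44.2% |

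The same model in fold changes uses an assumed log SD s of 0.8 to 1.0, 5 to 15% affected and a 5- to 10-fold shift m. The effective-sample fraction is s²/(s² + f(1−f)(ln m)²).
- Mildest case: 1/(1 + 0.0475 × 2.59) = 0.89.
- Worst case: 0.64/(0.64 + 0.1275 × 5.30) = 0.49.

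**4. Bias and chance imbalance.** Affected status precedes randomisation, so the expected difference between arms is nil. Simulated type I error for the t-test (20,000 runs per scenario; 10 or 20% affected, shifts of 2 or 3 SD) was 4.8 to 5.1%. With 8 affected among 80 split 40/40, the hypergeometric chance of 6:2 or worse is 26%. A 6:2 split alone moves the log-mean difference by (4/40) × ln m. That is a geometric mean ratio of 1.17 for a 5-fold shift and 1.26 for a 10-fold shift.

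**5. What the preoperative sample can recover.** Assume a correlation of 0.5 between preoperative and postoperative log values.
- If the shift is the same before and after surgery, it cancels in the change from baseline. The variance of the change is 2(1 − 0.5)s² = s², and power returns to 81%. For 10% affected and a 10-fold shift, the unadjusted t-test has about 58 to 64%.
- If the condition or drug alters only the response to surgery, nothing cancels. The variance of the change is s² + f(1−f)(ln m)², the same as unadjusted, and power stays at about 58 to 64%.

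**The case against.** The best reply is that the design already has a remedy. Table 1 plans a preoperative cytokine sample and the analysis section names repeated measures ANOVA, whose group-by-time term compares within-patient change. A patient who is high before surgery and equally high afterwards does little harm. The rank test, also allowed, softens the effect of extreme values: about 64 to 66% power in the 10%, 10-fold case. Cytokines are secondary, every size above is assumed, and broad eligibility has its own value for a pragmatic question. Nothing shows how many such patients this single hospital would enrol.

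Most of that stands, and it limits the point to precision. It does not remove it. The baseline sample does not help where the response to surgery is altered, as a steroid may do. No use of the baseline value is stated, and the Data collection section omits that sample. Nor are the affected conditions sure to act in one direction: infection and immunosuppression may pull opposite ways, which the single-shift model above ignores.

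A reader might also infer that cortisol-secreting adrenal tumours are a planned part of the population, since several cited operative series are adrenalectomy series. The protocol does not name adrenal surgery as an indication. Such patients are admitted only by silence, so a specific exclusion for them would be speculative.

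**Conclusion.** The omission is real and no other section closes it. It costs precision and ease of interpretation in a secondary outcome named in the objective. The size cannot be calculated from the protocol. Under the assumptions above, with 5 to 20% of patients affected, it runs from about two points of power to a loss of more than a third of it (81% to 44%) for an unadjusted comparison, and less where the preoperative value is used and the disturbance is stable.

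Two stronger readings are tempting. One is that pre-existing disease will swamp the anaesthetic effect; no figure in the protocol shows this, and a small share or a modest shift costs only a few points. The other is that the cytokine comparison is biased or more prone to false positives; randomisation gives no expected bias, type I error stays near 5%, and an uneven split is ordinary chance imbalance that the p-value already allows for. The primary outcome and the 40 per arm are unaffected. Severity is minor to moderate.

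**What to change.** Add two items to the Exclusion criteria:
- active infection, including urinary tract infection, at the preoperative visit;
- autoimmune or chronic inflammatory disease, or current systemic corticosteroid or immunosuppressant use.

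Both can be judged from the routine preoperative history and tests. The cost is a protocol amendment to one list, slightly slower recruitment and a somewhat narrower population. No extra patients or procedures are needed. If the sponsor prefers to keep the population broad, the minimum is to record these conditions at baseline and prespecify a sensitivity analysis without the affected patients.

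In either case, compare cytokines on a suitable scale with adjustment for the preoperative value. Also reconcile the Data collection section (2, 6 and 24 h only) with Table 1 (preoperative sample as well), so that the baseline sample is certain to be taken. As Table 1 already schedules that sample, this costs only wording.
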